### Study population

All patients with a femoral neck fracture who are admitted to Danderyd Hospital during the inclusion period will be screened for participation in the study and those who agree to participate and provide written informed consent will be included. The inclusion criteria are an acute displaced femoral neck fracture (Garden stage III or IV) that had been sustained within the previous thirty-six hours, an age of eighty years or more [20], an ability to walk indoors and outdoors with or without the help of walking aids and an absence of cognitive dysfunction (Pfeiffer test 8–10 points) [21]. Exclusion criteria includes patients with osteoarthritis or rheumatoid arthritis in the fractured hip, pathologic fractures, non-walkers, severe cognitive impairment (Pfeiffer test 0–7), and contraindications for surgery by other reasons (ulcers, severe somatic illness, severe bleeding disorder) and those who were unsuitable to participate in the trial for any other reason (i.e. psychiatric disease, alcoholism).

A detailed inclusion and exclusion list is presented in Table 1. The inclusion period is planned from 2009–2016. End of study (EOS) will be at the last included patient’s last visit in 2026 (Fig. 1, Table 2).

**Table 1 Tab1:** Detailed inclusion and exclusion criteria

Inclusion criteria	
1. Age above 80 years.	
2. Acute (<36 h) displaced femoral neck fracture (Garden ≥3).	
3. Independent walking ability with or without walking aids.	
4. Pfeiffer test 8–10 points.	
Exclusion criteria	
1. Osteoarthritis or rheumatoid arthritis in the fractured hip	
2. Pathologic fractures	
3. Non-walkers	
4. Cognitive impairment (Pfeiffer Test 0–7)	
5. Contraindications for surgery by other reasons (ulcers, severe somatic illness, severe bleeding disorder).	
6. Unsuitable to participate in the trial for any other reason.

**Table 2 Tab2:** Secondary endpoints

No.	Measurement	Follow-up time
1	Baseline data including height, weight, medical history, physical examination	Screening
2.	Pain Numerical Rating Scale (PNRS)	Screening, 3 months, 1, 2, 4, 6 and 10 years
3.	Complications	Screening, 3 months, 1, 2, 4, 6 and 10 years
4	Reoperations	Screening, 3 months, 1, 2, 4, 6 and 10 years

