### Endpoints and follow-up

The primary endpoint variable will be patient-reported functional hip status assessed with Harris hip score [23–25] and health related health-related quality of life assessed by the EQ-5D (EuroQoL) at 2 years. EQ-5D uses five dimensions: mobility, self-care, usual activity, pain/discomfort and anxiety/depression [26].

Secondary endpoints include functional scores at the other follow-up times and pain in the operated hip evaluated with VAS (Visual Analogue Scale [27], surgical time and blood loss, erosion of the acetabular cartilage in patients treated with hemiarthroplasty (evaluated according to Baker et al. [11]).

The study period is 10 years. Follow-up will be performed at 3 months, 1, 2, 4, 6 and 10 years. First study results will be reported after the last patient enrolled in the study has been followed for 2 years.

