### Statistics

The analyses will be performed on the basis of the intention-to-treat principle, and all patients who are allocated to either group will be included in the analysis, regardless of actual surgery performed. Descriptive statistics (means and standard deviations) will be used to describe the patient characteristics and outcome variables at the measurement points. We will use the Student’s t-test and Levene’s test for comparison of Harris hips score and EQ-5D between the groups. An analysis of covariance (ANCOVA) of the primary endpoint will also be used to reduce variance, adjusted for exposure variable (total hip arthroplasty/hemiarthroplasty) and stratification (male/female). For subjects that withdrawn from the study before completion, the data from the last observation will be carried forward (imputed). The analyses will be performed with SPSS 22.0 for Windows (SPSS, Chicago, Illinois) statistical software.

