### Study design

The internal validity of this trial is good due to the strict inclusion criteria, recruitment procedure and rigorous follow-up. However, some difficulties regarding blinding must be mentioned. Postoperative X-rays will reveal the type of allocation for the investigators. However, patients are blinded to their treatment and thus would not affect the patient reported outcome.

The exclusion criteria can affect the external validity and generalizability due to the fact that a large number of patients will be excluded from the trial. However, the exclusion criteria are mainly focusing on excluding patients with either a malignant disease or those with contraindications for either treatment methods.

We have chosen the primary end-point to be evaluated at several follow-up periods postoperatively, to be able to detect differences in rehabilitation and during short to medium term. We expect that the effect of acetabular erosion may influence the results of hemiarthroplasty at follow-up after the 1 year follow-up.

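### The ANCOVA meant to reduce variance adjusts for sex alone, which probably removes little; other baseline predictors already on record should be prespecified

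*Protocol article*

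**What the plan says.** The Statistics section of the protocol article names two analyses. The first is unadjusted: "We will use the Student’s t-test and Levene’s test for comparison of Harris hips score and EQ-5D between the groups". The second is an analysis of covariance of the primary endpoint, which "will also be used to reduce variance, adjusted for exposure variable (total hip arthroplasty/hemiarthroplasty) and stratification (male/female"). Sex is also the stratification factor in Randomization and blinding.

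Endpoints and follow-up sets the primary time point, ending with "health related health-related quality of life assessed by the EQ-5D (EuroQoL) at 2 years", and adds that "Secondary endpoints include functional scores at the other follow-up times". The Discussion, under Study design, says "We have chosen the primary end-point to be evaluated at several follow-up periods postoperatively".

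For screening, the first row of Table 2 reads "Baseline data including height, weight, medical history, physical examination". That table is titled "Secondary endpoints". The eligibility criteria admit patients who walk with or without aids, from 80 years upward with no upper age limit.

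The article describes no pre-fracture Harris hip score or EQ-5D. Nor does it say that none is collected.

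**The concern.** Adjustment narrows the confidence interval only to the extent that the covariates predict the outcome. The plan states the aim of reducing variance and then lists a single covariate, chosen because it is the stratifier. Age and walking ability before the fracture differ between patients by design of the eligibility criteria, and either could be expected to bear on hip function two years later. Neither is named.

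The stake is precision. The sample size section plans for as few as 40 evaluable patients per arm out of 60 randomized. At that size a modest predictor changes power by a few percentage points, while a weak one changes almost nothing.

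**Working it through.** **Inputs from the article (Sample size):** difference 10 points, SD 15, two-sided test, significance level 0.025, 40 evaluable and 60 randomized per arm.

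**Assumed, because the article gives no value:** the sex difference in the 2-year Harris hip score, the share of the less frequent sex, and the correlation r of added baseline predictors with the 2-year score.

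**1. The plan's own figure.** For a two-sample t-test with n per arm, power comes from the noncentral t distribution with 2n − 2 degrees of freedom and noncentrality (10/SD) × √(n/2). With SD 15, n = 40 and level 0.025, the noncentrality is 0.667 × √20 = 2.98 and power is 75.5%, against the stated 80%. Reaching 80% needs 44.05, so 45 per arm. At two-sided 0.05, power at 40 per arm is 83.8%. The stated 40 per arm at 80% is therefore not reproduced at either level. That is a separate matter; 75.5% serves here only as the starting point.

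**2. What sex can remove.** With a share p of one sex and a mean difference d between the sexes, sex accounts for p(1 − p)d² of the total variance of 15² = 225.

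| d (assumed) | p (assumed) | Variance removed | Share of 225 | Residual SD | Power, 40 per arm |
|---|---|---|---|---|---|
| 2 | 0.2 | 0.64 | 0.3% | 14.98 | 75.7% |
| 2 | 0.5 | 1.00 | 0.4% | 14.97 | 75.8% |
| 5 | 0.2 | 4.00 | 1.8% | 14.87 | 76.4% |
| 5 | 0.5 | 6.25 | 2.8% | 14.79 | 76.8% |
| 10 | 0.2 | 16.0 | 7.1% | 14.46 | 78.9% |
| 10 | 0.5 | 25.0 | 11.1% | 14.14 | 80.8% |

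Sex helps materially only if men and women differ by about as much as the treatment effect the trial is designed to detect.

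**3. What other baseline predictors could remove.** Residual SD = 15 × √(1 − r²), where r is the correlation of the added covariates, taken together, with the 2-year score.

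| r (assumed) | Variance removed | Residual SD | Power, 40 per arm | Power, 60 per arm |
|---|---|---|---|---|
| 0 | 0% | 15.0 | 75.5% | 91.5% |
| 0.2 | 4% | 14.7 | 77.4% | 92.6% |
| 0.3 | 9% | 14.3 | 79.8% | 93.9% |
| 0.4 | 16% | 13.7 | 83.1% | 95.5% |

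These figures ignore the one degree of freedom spent on each covariate, which is negligible beside 78 residual degrees of freedom.

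**4. Comparison.** At 40 per arm, sex with a difference of up to 5 points adds at most 76.8 − 75.5 = 1.3 percentage points. Predictors with r of 0.2 to 0.4 add 1.9 to 7.6 points. If all 60 per arm are analysed, the same predictors add 1.1 to 4.0 points.

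**The case against.** The strongest reply is that nothing here is an error. Adjusting for the stratification factor is conventional, it is prespecified, and the t-test is named first. In a randomized trial, chance imbalance in prior function does not bias the estimate, and the t-test's standard error already allows for it. The correlations are assumed. The 75.5% starting point is low partly because the stated sample size does not match the stated level. More than 40 per arm may be analysed, since 60 are randomized and last observations are carried forward. All of this stands. It limits the point to an inexpensive improvement, and the gain reaches only conclusions drawn from the ANCOVA.

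A reader might go further and infer that neither primary outcome has a pre-fracture value. The article does not support that. Table 2 lists secondary endpoints, its baseline row is worded openly, and a condensed article may leave the full list of baseline assessments to the full protocol.

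A reader might also object to pain at screening as a baseline, because it is taken within 36 hours of a fracture. No section uses it as a covariate or as the start of a change score, so there is nothing to correct. Nor is pain the only outcome scheduled at screening: Table 2 gives complications and reoperations the same schedule.

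Finally, walking-aid status may not have been recorded, since the criterion is met with or without aids. That is why the proposal applies only where it is on record.

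**Conclusion.** The point holds as a minor one. The stated purpose of the ANCOVA is weakly served by its only covariate unless sex strongly predicts the Harris hip score. For assumed sex differences of 2 to 5 points, adjustment removes 0.3% to 2.8% of the variance and power at 40 per arm stays at or below 76.8%. Baseline predictors with a correlation of 0.2, 0.3 or 0.4 would bring it to about 77%, 80% or 83%.

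These sizes rest on the article's SD of 15, difference of 10 and two-sided 2.5% level, and on sex effects and correlations that the article does not give. The gain is smaller if more than 40 per arm are analysed. It is a gain in precision; the analysis as planned is not biased for want of these covariates.

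**What to change.** Before the 2-year analysis, and without sight of results by arm, extend the ANCOVA sentence in the Statistics section. Alongside treatment and sex, name age, pre-fracture walking-aid status where it was recorded at inclusion, and any pre-fracture Harris hip score or EQ-5D that the case report form already holds. State in the same place how missing covariate values will be handled.

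The cost is one line of text, plus a few missing covariate values to handle and at most some retrieval from existing records. First results are due only once the last enrolled patient has been followed for 2 years, so there is time to prespecify this.

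Adding recalled questionnaires at screening is not proposed. Inclusion runs from 2009 to 2016 and the article appeared in October 2015, so most patients would lack the value.

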### When and how to withdraw subjects from the trial

Should a subject request or decide to withdraw from the study, all efforts will be made to complete and report the observations as thoroughly as possible up to the date of withdrawal. For withdrawn subjects the last post-baseline observation will be carried forward. In a case of withdrawal of full consent, the subject will be followed according to the routine standard follow-up of arthroplasty patients at our institution, including regular clinical examinations and radiographic follow-up visit at the operating surgeon every 2–3 years.

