### Sample size

Prior to the commencement of the study, a two-sided power analysis has been performed. We will test the null hypothesis that the mean Harris hip scores for the two groups will be equal. We assume that a mean difference of 10 points (standard deviation, 15 points) [4] in the Harris hip score is the smallest effect that will be clinically relevant. We calculate that a total of 80 patients (40 in each group) will have a power of 80 % to yield a significant result.

This calculation also allows a 80 % power to prove non-inferiority (non- difference) of the secondary endpoint EQ-5D with a sample of 40 patients in each group with the assumption of an EQ-5D value of 0.73 with standard deviation 0:18. The significance level was set at a conservative 2.5 % (p <0.025) because we have two sample size calculations. We will include 60 patients in each group (120 total) to allow for loss to follow-up.

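### Carrying the last observation forward is the only rule for withdrawn patients, so the 2-year comparison can be filled with 3-month and 1-year scores that predate the expected late effect

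*Protocol article*

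**What the plan says.** The rule appears twice in the protocol article. Under Statistics: "For subjects that withdrawn from the study before completion, the data from the last observation will be carried forward (imputed". Under the section on withdrawal of subjects: "For withdrawn subjects the last post-baseline observation will be carried forward". No other primary method for incomplete follow-up is given.

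Four other statements bear on it:

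- **Endpoint.** Under Endpoints and follow-up, the primary endpoint is the Harris hip score together with "health-related quality of life assessed by the EQ-5D (EuroQoL) at 2 years".
- **Visits.** The same section says: "Follow-up will be performed at 3 months, 1, 2, 4, 6 and 10 years".
- **Expected course.** The Discussion, under Study design, explains that several visits are used "to be able to detect differences in rehabilitation and during short to medium term". It adds: "We expect that the effect of acetabular erosion may influence the results of hemiarthroplasty at follow-up after the 1 year follow-up".
- **Numbers.** Sample size asks for 40 patients per group and then says: "We will include 60 patients in each group (120 total) to allow for loss to follow-up". Statistics promises that "all patients who are allocated to either group will be included in the analysis, regardless of actual surgery performed".

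**The concern.** Carrying a score forward assumes that nothing changes after the patient leaves. The article's own account of the course argues against that assumption. The early visits are there partly to follow rehabilitation, and one mechanism that could separate the groups is expected only after the 1-year visit. A value carried to 2 years cannot contain that late change.

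Three things are at stake:

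- The 2-year estimate becomes a mixture of the 2-year difference and earlier differences.
- Carried values enter the t-test and the ANCOVA as if they had been observed, so the standard error takes no account of the imputation.
- The article also seeks a non-inferiority or no-difference conclusion on EQ-5D. There, shrinkage towards zero is not a cautious error.

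This is not a detail left to a fuller document. The article names the method in two sections.

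**Working it through.** **Inputs from the article.** Difference 10 points, SD 15, two-sided test, significance level 0.025, 40 evaluable and 60 enrolled per group (Sample size). Endpoint at 2 years, earlier visits at 3 months and 1 year (Endpoints and follow-up).

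**Inputs assumed.** *f*, the share of 2-year values that are carried, and *e*, the between-group difference at the visit they come from. The article gives neither.

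**Step 1: the plan's own figure.** n per group = 2 (z₁₋α/₂ + z₀.₈₀)² × 15² / 10².

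- At α = 0.05: 2 × (1.960 + 0.842)² × 2.25 = 35.3, so 36 (37 with the t distribution). With 40 per group, power is 83.8 % (t).
- At α = 0.025: 2 × (2.241 + 0.842)² × 2.25 = 42.8, so 43 (45 with the t distribution). With 40 per group, power is 75.5 % (t).

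Forty per group at 80 % is matched by neither level. That is a separate matter and does not affect this point.

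**Step 2: the loss allowance.** 1 − 40/60 = 33 %. This is an upper bound implied by the two sample sizes, not a stated loss rate.

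**Step 3: dilution.** Expected difference = (1 − f) × 10 + f × e. Power is t-based at α = 0.025 with SD 15 kept. It uses 60 per group when values are carried forward and 60 × (1 − f) per group when only observed 2-year scores are used. The observed-score analysis keeps the 10 points if loss is at random.

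| f | e | Expected difference, carried forward | Power, carried forward | Power, observed scores only |
|---|---|---|---|---|
| 33 % | 0 | 6.7 | 56.6 % | 75.5 % |
| 33 % | 2.5 | 7.5 | 68.0 % | 75.5 % |
| 33 % | 5 | 8.3 | 77.9 % | 75.5 % |
| 33 % | 7.5 | 9.2 | 85.8 % | 75.5 % |
| 33 % | 10 | 10.0 | 91.5 % | 75.5 % |
| 20 % | 0 | 8.0 | 74.2 % | 83.7 % |
| 20 % | 5 | 9.0 | 84.4 % | 83.7 % |
| 10 % | 0 | 9.0 | 84.4 % | 88.1 % |
| 10 % | 5 | 9.5 | 88.3 % | 88.1 % |

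**Step 4: two visit patterns.** Assume 17 % are lost after 3 months and 16 % after 1 year.

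- Effects 0, 2 and 10 points at the three visits: 0.17 × 0 + 0.16 × 2 + 0.67 × 10 = 7.0 points.
- Effects 5, 7 and 10 points: 0.17 × 5 + 0.16 × 7 + 0.67 × 10 = 8.7 points.

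Simulation with 60 per group, SD 15, visit correlation 0.6 and α = 0.025 gives the same estimates. For the first pattern, power is 60 % carried forward against 75 % with observed scores. For the second it is 81 % against 76 %. The estimate is diluted in both, but nominal power moves in opposite directions, because carried values count as observed.

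**Step 5: unequal loss, no true effect.** If early scores lie *m* points below 2-year scores, bias = m × (difference in the share carried). With m = 5 and 20 % against 30 % carried, this is 5 × 0.10 = 0.5 points. With m = 10 and 15 % against 35 %, it is 10 × 0.20 = 2 points. The sign depends on which group loses more patients early.

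**Step 6: a gap in the rule.** A patient lost before 3 months has no post-baseline score to carry, so the rule cannot by itself deliver the promise to analyse everyone allocated.

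**The case against.** The case for the plan has real force on scope and size.

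**Early effects are not ruled out.** The article says only that erosion may influence results after 1 year, and it also looks for differences during rehabilitation. A reader might infer that each carried value contributes no effect at all. The documents do not support that; it is the e = 0 rows above. If the early difference equals the 2-year difference, nothing is diluted, and if it is larger, the estimate is inflated.

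**One third is a ceiling.** It covers all loss, whereas the rule is written for withdrawals. If 20 of 60 per group are lost but only 6 have carried values, the estimate is (40 × 10 + 6 × 0)/46 = 8.7 points, or (40 × 10 + 6 × 5)/46 = 9.35 points with an early difference of 5.

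**Deaths.** At age 80 and over, a reader might infer that a patient who dies keeps a living score, or that the later visits would consist mostly of old values. Neither section mentions death and no mortality rate is given, so both remain inferences.

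**Type I error.** With 6 points of recovery after 3 months, it reached only 3.6 to 3.9 % in simulations with 20 percentage points more early loss in one group. At 10 points it stayed at the nominal 2.5 %. Nothing in the article points to an imbalance of 20.

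**Superiority.** For the Harris hip score, shrinkage towards zero does not create a false benefit.

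All of this stands as a limit on magnitude. None of it defends the method as the sole primary approach to a 2-year estimate.

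**Conclusion.** The point holds for the choice of method. For withdrawn patients the article fixes a rule under which every imputed 2-year score comes from 3 months or 1 year, before the period in which it expects that erosion may act.

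If the carried difference is smaller than the 2-year difference, the estimate shrinks. A true 10 points becomes about 7 to 9 points (6.7 to 9.2 for a carried difference of 0 to 7.5) at the full one-third allowance. At 10 % carried it becomes 9.0 to 9.5 points for a carried difference of 0 to 5. These figures rest on assumed loss and early effects. The observed-score comparison also assumes that loss is at random.

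A general loss of power is not shown. With SD 15 kept, nominal power under carrying forward matches or exceeds that of observed scores once the carried difference is about 5 points. Unequal loss can bias the estimate in either direction.

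For EQ-5D, shrinkage makes a no-difference conclusion easier to reach. Read as one-sided non-inferiority, it helps when the tested treatment is truly worse at 2 years. No size was calculated for EQ-5D.

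**What to change.** Replace carrying forward as the primary method with a mixed model for repeated measures on the 3-month, 1-year and 2-year scores. Include treatment, visit, treatment by visit, and sex as the stratification factor. Name the 2-year treatment contrast as the primary estimate for the Harris hip score and for EQ-5D, with no single imputation. Amend both sections that state the present rule. Keep carrying forward at most as a sensitivity analysis.

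State that the rule for withdrawals does not apply to scores after death, and report mortality by group beside the scores so that readers can see who contributes to the comparison.

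The cost is a change of wording and a mixed-model procedure in the same software; no new data are needed. The downside is that the model relies on a missing-at-random assumption, which should be checked by sensitivity analysis. Its performance was not simulated here; the comparison above is with a simple analysis of observed 2-year scores.

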## Discussion

### Rationale for the study

Whether to choose hemiarthroplasty or total hip arthroplasty in the treatment of displaced femoral neck fractures in the most elderly and fit patients are often debated. Despite indications that total hip arthroplasty yields a better patient reported outcome, it is plagued with an increased risk for prosthetic dislocation and thus revision surgery in patients with cognitive impairment. The frequency of patients with manifest or impending cognitive impairment increases with age and thus the risk for complications. The previously published studies in the field have a heterogeneity across the included selection of patients and distinct subgroup effects [18]. There is a lack of level one evidence regarding the choice of arthroplasty in the fit most elderly patients.

